# １６．Matters related to access to source documents, etc.

In this study, source documents are defined as the following.

①Records of researcher consent and information provision

②Medical records, clinical examination data and imaging films, etc., data at the time of case registration, and the original records of case reports

The principal investigator and the implementing medical institution will provide direct access to all clinical research-related records, including source documents, during monitoring and auditing related to clinical research, as well as during investigations by accredited clinical research review committees and regulatory authorities.

# １７．Periodic reporting

The Principal Investigator shall, in principle, report to the Accredited Clinical Research Review Committee on the following details concerning the implementation of this research every year from the date of submission of the protocol to the Minister of Health, Labor and Welfare, and within two months after the expiration of said period. Use the Uniform Form 5 Periodic Report and Appendix Form 3 Periodic Report.

①Number of research subjects who participated in this study

②Occurrence and subsequent progress of severe adverse effects related to this study

③Occurrence of noncompliance with the ministerial ordinance or research protocol pertaining to this research and subsequent actions

④Evaluation of the safety and scientific validity of this study

⑤Matters concerning the involvement of pharmaceutical manufacturers and sellers, etc. in this research

In addition, within one month from the date on which the Accredited Clinical Research Review Committee gives its opinion, the following information shall be reported to the Minister of Health, Labor and Welfare using the attached Form 3.

①Name of the authorized clinical research review committee described in the implementation plan

②Approval or disapproval of the continuation of this research by the Accredited Clinical Research Review Committee

③Number of subjects who participated in this study

　The principal investigator shall provide information to the principal investigator regarding the contents of the periodic report and its approval by the committee and submission to the Minister of Health, Labor and Welfare. In addition, the principal investigator and each principal investigator shall report to the administrators of their respective medical institutions by means of the aforementioned periodic reports.

# １８．Status of conflicts of interest related to research and other research, including sources of funding for research, conflicts of interest related to research for the duration of the research, and personal earnings

This research is planned to be carried out with 5 million yen from the Okayama University Academic Fund.

In addition, the principal investigator shall declare any conflicts of interest in accordance with the "Guidance for the Management of Conflicts of Interest in Clinical Research Law" and obtain its review and approval. In addition, whether there is any change in the conflict of interest of the research and the conflict of interest of individuals shall be checked at the time of periodic reporting and reported to the Accredited Clinical Research Review Committee.

# １９．Methods of disclosing information about research (registration of research plans and publication of research results)

This study is registered in the Japan Registry of Clinical Trials (jRCT: https://jrct.niph.go.jp/), a system for disclosing clinical research implementation plans and research summaries. The results obtained in this study will be presented on the jRCT and at various related conferences, such as the Japanese Society of Internal Medicine, and will be published as papers in professional journals.

# ２１．Procedures for obtaining informed consent from a surrogate, etc.

In this study, no surrogate will be established.

# ２２．Procedures for obtaining informed consent (including explanation items and methods)

　Not applicable for this study.

# ２３．Procedures to ensure that all requirements for research in situations of urgent and apparent life threatening situations are met.

　Not applicable for this study.

# ２４．Details of any financial burden or gratuity to the research subjects, if any

# In accordance with the administrative notice "Treatment of Publicly Funded Medical Care for Novel Coronavirus Infections" issued on March 4, 2020, this treatment is intended for patients who are COVID-19 positive, and since it will be conducted as publicly funded medical care, there will be no cost burden to the research subjects.

In addition, there will be no honorarium for participating in this study.

# ２５．Response to adverse events and problems

（１）Definition of adverse events and problems

Adverse effects refer to illness, disability, death, or infection suspected to be caused by the conduct of the specified clinical research, as well as malfunctions that could cause these.

（２）Severe adverse events

　Serious adverse events are defined as follows.

　１）Death or threatened death

　２）the following adverse events

①　Cases that require hospitalization or extension of hospital stay at a medical institution for treatment

②　Cases that cause permanent disability

③　Adverse events that may lead to disability, etc.

④　① to ③, and death and side effects that are as serious as those that may lead to death.

⑤　Congenital diseases or abnormalities in the later generations

（３）Causal relationship with research

The relationship of all adverse events to the conduct of the study or to the treatment under study will be determined by the principal investigator, principal investigator, or sub-investigator. In addition to the temporal relationship to the initiation of the study treatment, the determination will take into account the course of the underlying disease, complications, concomitant medications, study procedures, accidents, and other external factors.

（４）Predictability

Predictability of adverse events should be determined based on the package insert and interview form. If the nature, severity or frequency of an adverse event is inconsistent, it should be considered an unknown adverse event. Predictable adverse events and failures include elevated AST/ALT (<0.1-5%) and others (constipation, diarrhea, nausea, dry mouth, abdominal pain, abdominal distention, headache, rash, pruritus, elevated total cholesterol, eyelid redness/heat, etc.) all <0.1%.

（５）Outcome

The principal investigator and sub-investigators (principal investigators, etc.) will provide appropriate treatment and therapy for all illnesses that occur, and will conduct follow-up studies until symptoms disappear or laboratory values return to baseline or pre-administration values, or until the principal investigator, etc. determines that follow-up is not medically necessary. The outcome of adverse events and failures will be classified as follows: 1) recovery (disappearance or recovery of symptoms, findings, and laboratory values), 2) minor recovery (reduction of the event in question), 3) unrecovered (no change to worsening), 4) death, and 5) unknown.

（６）Responsibilities of principal investigators, etc. (reporting of serious adverse events)

① If a principal investigator, etc. becomes aware of the occurrence of a serious illness, etc. in the conduct of specified clinical research, he/she shall take the necessary measures, including explanation and treatment of the research subjects, etc.

② When a principal investigator, etc. becomes aware of the occurrence of a disease, etc., he/she shall report to that effect to the administrator of the medical institution and then, pursuant to the provisions of Ordinance of the Ministry of Health, Labour and Welfare, report to that effect to the accredited Clinical Research Review Committee described in the implementation plan of said specified clinical research using the Uniform Form 8.

③ When a principal investigator becomes aware of any matter concerning the occurrence of a disease, etc. suspected to be caused by the conduct of specified clinical research, which is specified by an Ordinance of the Ministry of Health, Labour and Welfare (see the table below), the Principal Investigator shall report to that effect to the Minister of Health, Labour and Welfare using the attached Form 2-1 (Drugs), as specified by an Ordinance of the Ministry of Health, Labour and Welfare.

| Predictability | Adverse events | Report to the Accredited Clinical Research Review Committee | Report to the Minister of Health, Labor and Welfare |
| --- | --- | --- | --- |
| Unpredictable | Death or may lead to death | within 7 days | within 7 days |
|  | other adverse events | within 15 days | within 15 days |
| Predictable | Death or may lead to death | within 15 days | at periodic reporting |
|  | other adverse events | at periodic reporting | at periodic reporting |

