# ５．Observation and test items

（１）Clinical characteristics of the enrolled patients

　　Age, gender, current medical history, comorbidities, previous medical history, smoking history, height, weight, and Concomitant medication/concomitant treatment

（２）Inspection Items

Blood count (WBC, white blood cell image)、

Biochemical test（AST、ALT、LDH、TP、Na、K、Cl、BUN、CRP、PCT、KL-6）

Chest X-ray、chest CT、SpO_2_

Biomarkers (using residual serum from routine blood collection) Comprehensive cytokine analysis using multiplex system, Hydropeoxides, TRX-1 and HMGB-1, HSP70, S100A8/A9

（３）Check for adverse events and side effects

The details of adverse events, time of onset and resolution, degree, treatment, outcome, severity assessment, and relationship to teprenone medication should be described in the CRF. If necessary, follow-up will be conducted until the time when isolation, including home isolation, is lifted.

| Item/period of inspection/investigation | Screening  (within 7 days before registration)Scre | Registration | Intervrnyion | | | | | follow up | | at the timing of intubation |
| --- | --- | --- | --- | --- | --- | --- | --- | --- | --- | --- |
|  |  |  | Day1 | Day3 | Day5 | Day7 | Day10 | Day14 | Day21 |  |
| Eligibility verification and registration |  | ● |  |  |  |  |  |  |  |  |
| COVID-19 PCR | ○ |  |  |  |  |  |  |  |  |  |
| clinical examination |  |  |  |  |  |  |  |  |  |  |
| blood count and biochemistry | ○ |  | ● |  | ▲ |  | ▲ | ▲ | ▲ | ▲ |
| KL-6・ | △ |  |  |  |  |  |  |  |  |  |
| procalcitonin |  |  |  |  |  |  |  |  |  |  |
| temprature | ○ | ● | ● | ● | ● | ● | ● | ▲ | ▲ | ● |
| dose of oxygen | 〇 |  | ● | ● | ● | ● | ● | ▲ | ▲ | ● |
| SpO2 | ○ |  | ● | ● | ● | ● | ● | ▲ | ▲ | ● |
| biomarker |  |  |  |  |  |  |  |  |  |  |
| Serum storage for biomarkersseru |  |  | ▲ |  | ▲ |  | ▲ |  |  |  |
| effect determination |  |  |  |  |  |  |  |  |  |  |
| chest X-ray | △ |  |  | ▲ |  |  | ▲ |  | ▲ | ▲ |
| chest CT | △ |  |  |  |  |  | ▲ |  | ▲ | ▲ |
| toxicity assessment |  |  |  |  |  |  |  |  |  |  |
| Subjective and subjective symptoms |  |  | ● | ● | ● | ● | ● | ● | ▲ | ▲ |

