For the primary endpoint of endotracheal intubation rate, if the null hypothesis "the rate of endotracheal intubation in the non-treated group is equal to the rate of endotracheal intubation in the treated group" is rejected, it was judged to be effective. If not, it is considered invalid from a clinical medical standpoint. The significance level for the entire study is set at 10% on one side. No adjustment for multiplicity will be made.

【Efficacy analysis 】

The analysis of efficacy is based on the treatment assigned to the patients by the minimization method according to the intention-to-treat (ITT) principle. An ITT analysis is defined as a method of analysis based on the assignment of a treatment group to a treatment or non-treatment group that is determined prior to the initiation of the intervention, rather than on the actual intervention performed. For example, patients who are assigned to the treatment group but never receive treatment for some reason are treated as the treatment group.

Analysis of the primary endpoint (endotracheal intubation rate)

1. Method of main analysis

Based on the observed endotracheal intubation rate, a binomial test will be performed for the null hypothesis that "the rate of endotracheal intubation in the non-treated group is equal to the rate of endotracheal intubation in the treated group. The competing hypothesis will be "the tracheal intubation rate of the treated group is less than that of the non-treated group". If the null hypothesis is rejected, the test is considered valid; if not, the test is considered clinically invalid. The risk ratio is calculated by dividing the risk of tracheal intubation in the treated group by the risk of tracheal intubation in the non-treated group. The exact 90% confidence interval based on the binomial distribution will be used to estimate the interval of the risk ratio.

1. Subgroup analysis will be conducted based on the factors described below.

＜Factors for which subgroup analysis is planned＞

Under 70 years old / Over 70 years old ・ Male / Female ・ Smoking history/No smoking history

Analysis of secondary endpoints (mortality)

The analysis will be performed in the same way as for the primary endpoint.

【Safety analysis】

Calculate the number and percentage of patients in the CTCAE version 5.0 Grade 1 to Grade 5 groups in the treated and non-treated groups, respectively.

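### Section 25(1) builds suspected causality into the definition of an adverse event, contradicting sections 25(3) and 5(3) and leaving it unclear what sites must record, above all in the untreated arm

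*Protocol*

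**What the plan says.** Section 25(1) of the protocol stands under a heading that announces the definition of adverse events and problems. Its text reads: "Adverse effects refer to illness, disability, death, or infection suspected to be caused by the conduct of the specified clinical research". It also covers malfunctions that could lead to such outcomes. Section 25(2) then sets out seriousness, but no other place in the protocol says what an adverse event is.

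Other sections use the term as follows:

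- **Section 25(3), causality:** "The relationship of all adverse events to the conduct of the study or to the treatment under study will be determined". It adds that "the determination will take into account the course of the underlying disease, complications, concomitant medications, study procedures, accidents, and other external factors".
- **Section 5(3), collection:** the heading is "Check for adverse events and side effects". Among the details to be entered for adverse events it lists "severity assessment, and relationship to teprenone medication should be described in the CRF".
- **Section 6, endpoint 9:** adverse events by CTCAE version 5.0, with no causality condition.
- **Section 8, safety analysis:** "Calculate the number and percentage of patients in the CTCAE version 5.0 Grade 1 to Grade 5 groups", for the treated and the non-treated group separately. The safety population includes control patients who took no teprenone.

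**The concern.** A definition decides what enters the data. If suspected causality is part of the definition, an event judged unrelated is not an adverse event and need not be recorded. If causality is judged afterwards, every event is recorded and then classified. The protocol contains both rules.

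The choice matters more here than in a blinded placebo trial. Treatment is open-label (section 4(1)), and the control arm receives no study drug. Staff know the arm, and section 25(4) tells them which findings to expect from teprenone, including raised AST/ALT, diarrhoea and nausea. The same finding may be suspected, and so recorded, in a teprenone patient, and put down to COVID-19 and left out in a control.

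The control arm's role in the safety table is to show how often such findings occur without the drug. If recording differs by arm, the difference in the table mixes any drug effect with the recording rule. No later analysis can restore events that were never entered.

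**Working it through.** The protocol gives no figure on this point. Its one design calculation, the power for the intubation rate, does not enter. The check is therefore a comparison of the passages, followed by a statement of what would be needed to size the effect.

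**Step 1. Does the definition contain a causality filter?** Yes. Section 25(1) requires suspicion that the conduct of the research caused the event. The sentence names adverse effects, but it stands under the heading for adverse events and is the only definition offered.

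**Step 2. Do other sections assume unfiltered recording?**

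| Section | Function | Causality filter on entry? |
|---|---|---|
| 25(1) | Definition | Yes |
| 25(3) | Causality judged for all adverse events, weighing underlying disease and concomitant medication | No; the step is redundant if unrelated events are already excluded |
| 5(3) | CRF content | No; relationship to teprenone is one attribute among several |
| 14(3) | Recording in the medical record and CRF once an event is recognised | No |
| 5, schedule | Symptom check required on Days 1, 3, 5, 7, 10 and 14 | No, and no distinction by arm |
| 6, endpoint 9 | CTCAE adverse events | No |
| 8 | Counts and percentages by grade and arm | No |
| 25(6) | Trigger for reporting to the Minister | Yes, with wording close to 25(1) |

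Sections 25(1) and 25(3) cannot both describe the same set of events. Sections 5(3), 14(3), 6 and 8 use the term without defining it, so a site that asks what counts is led back to 25(1). No sentence says which rule governs the CRF.

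**Step 3. What happens if 25(1) is applied literally?** Let p be the true proportion of patients with a given finding, taken as equal in both arms (no drug effect). Let r_T and r_C be the proportions of those patients in whom it is recorded.

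Recorded difference = p × r_T − p × r_C = p × (r_T − r_C)

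This is zero when both arms are recorded alike. Under 25(1), r_C tends to fall below r_T, because a patient who receives no study drug offers fewer grounds for suspecting the research. The difference then moves against teprenone. True toxicity that is put down to COVID-19 would lower r_T and be hidden.

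**Step 4. Can it be sized?** No. The protocol gives neither p for the untreated arm nor any basis for r_T and r_C. The direction can be argued; the amount cannot be derived.

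**The case against.** The strongest reply is that 25(1) is a reporting definition and does not control the CRF. It opens the section that leads to the reporting duties in 25(6), where similar wording triggers the report to the Minister. It speaks of adverse effects, and loose use of neighbouring terms in a translated text is a plausible explanation. The sections that govern recording and analysis (5(3), 14(3), the required symptom checks, endpoint 9 and section 8) carry no filter and do not separate the arms. Section 25(5) also asks for treatment and follow-up of all illnesses that occur.

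Much of this stands, and it limits the point. A reader might infer that the untreated arm can have almost no adverse events by definition, or that the by-arm comparison is invalid. The protocol supports neither:

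- Both inferences need a site to put one sentence of 25(1) above all the unfiltered provisions.
- The condition in 25(1) is the conduct of the research, not teprenone, so a procedure-related event in a control could still qualify.
- Section 8 plans a descriptive table, with no test and no decision rule.
- A striking illustration can be built by assuming a 20% rate of some finding and 50 patients per arm: 20% of 50 is 10, so 10 against 10 could be recorded as 10 against 0, or as 0 against 0. The rate is invented, equal allocation is assumed, and both results require complete non-recording in at least one arm. They mark extremes and are not evidence of size.

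The objection does not remove the contradiction. Section 25(1) is not labelled as a reporting definition. It stands under a general heading and comes before rules on causality, predictability and outcome that apply to adverse events at large. Nor can the matter be left to a SAP, because it decides what sites enter. A descriptive table also misleads if recording differs by arm.

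**Conclusion.** The point holds as an internal contradiction with a possible bias. The protocol's only definition of an adverse event requires suspected causation by the research, while 25(3) and 5(3) require causality to be judged for events already recorded. Which rule governs CRF entry is not stated.

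The consequence is conditional. If unblinded sites apply 25(1) literally, untreated-arm events will tend to be under-recorded relative to the teprenone arm, and endpoint 9 and the section 8 table would be biased. If sites follow 5(3) and 14(3), the problem does not arise. The size cannot be computed from the document. The primary endpoint is not affected. The conclusion rests on the wording alone, and on the assumption that staff who know the arm suspect the research less often in patients who receive no study drug.

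**What to change.** Amend section 25(1) to state that, for CRF recording, endpoint 9 and the section 8 safety table, an adverse event is any untoward sign, symptom, disease or laboratory worsening from registration onward, in either arm and regardless of suspected cause. Causality is then judged afterwards, as 5(3) and 25(3) already require. Registration gives both arms the same starting point, which first dose cannot do when controls receive none.

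Keep the present causality wording, labelled as the definition for reporting under 25(6), so that the reporting duties do not change. The layout of the safety tables can stay with the SAP.

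The cost is a protocol wording change and slightly more recording in the control arm. It should be made before sites record further events, since omitted events may not be recoverable later.

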# ２６．Compensation for health damage and its details

# The drugs used in this study are those that are widely used in ordinary medical practice. In this sense, patients will not be exposed to risks that exceed those of routine medical care. Therefore, for any health damage caused by participation in this clinical trial, appropriate treatment according to the medical condition will be provided as insurance treatment, just as in normal medical care. In addition, the subjects of this study are COVID-19 positive cases, which are publicly funded medical care (issued on March 4, 2020, "Treatment of publicly funded medical care for novel coronavirus infection").In addition, no financial compensation such as a visitation fee or various allowances will be provided.

# ２７．Nonconformity Report

When the principal investigator becomes aware that the clinical research is not in compliance with laws and regulations or the research protocol (referred to as "noncompliance"), he/she shall promptly report it to the administrator of the research institution. When a research subcontracting physician becomes aware of nonconformity, he/she shall promptly report it to the principal investigator. When a investigator becomes aware of the occurrence of a serious adverse event, he must promptly notify the principal investigator. In addition, the principal investigator shall promptly provide the information to other investigators to that effect. In this case, said other investigators shall promptly report the contents of said information to the administrator of the medical institution. In the case that a nonconformity is found to be particularly serious, the principal investigator shall promptly obtain the opinion of an accredited clinical research review committee.

The term "serious nonconformity" refers to noncormity that may affect the human rights and safety of subjects of clinical research, as well as the progress of the research and the reliability of the results. For example, non-compliance with selection/exclusion criteria, discontinuation criteria, concomitant use of prohibited therapies, etc., does not include non-compliance with the research protocol to avoid immediate danger to the subjects of the clinical research or for other unavoidable medical reasons. If a serious noncompliance occurs, the principal investigator shall take measures to prevent its recurrence, inform the submitting investigator and other persons engaged in the clinical research concerned, and thoroughly prevent its recurrence. (3) At the time of regular reporting to the Committee, the occurrence of nonconformity with laws and regulations or the research protocol pertaining to the clinical research concerned and the subsequent response shall be reported.

